## Abstract

**Background:**

The raising prevalence of type-2 diabetes mellitus and obesity has been recognized as a major problem for public health, affecting both developed and developing countries. Impaired fasting plasma glucose has been previously associated with endothelial dysfunction, higher levels of inflammatory markers and increased risk of developing insulin resistance and cardiovascular events. Besides life-style changes, the blockade of the renin-angiotensin system has been proposed as a useful alternative intervention to improve insulin resistance and decrease the number of new type-2 diabetes cases. The aim of this clinical trial is to study the effect of the treatment with Candesartan, an angiotensin II receptor antagonist, on the insulin resistance, the plasma levels of adipoquines, oxidative stress and prothrombotic markers, in a group of non diabetic, non hypertensive, dysglycemic and obese subjects.

**Methods and design:**

A randomized, double blind, cross-over, placebo-controlled, clinical trial was designed to assess the effects of Candesartan (up to 32 mg/day during 6 months) on the Homeostasis Model Assessment (HOMA) index, lipid profile, protrombotic state, oxidative stress and plasma levels of inflammatory markers. The participants will be recruited in the "Fundación Cardiovascular de Colombia". Subjects who fullfil selection criteria will receive permanent educational, nutritional and exercise support during their participation in the study. After a 15 days-run-in period with placebo and life-style recommendations, the patients who have a treatment compliance equal or greater than 80% will be randomlly assigned to one of the treatment groups. Group A will receive Candesartan during 6 months and placebo during 6 months. Group B will receive placebo during the first 6 months, and then, Candesartan during the last 6 months. Control visits will be programed monthly and all parameters of interest will be evaluated every 6 months.

**Hypothesis:**

Treatment with Candesartan, could improve the HOMA index, the response to the oral glucose tolerance test and reduce the plasma levels of adipoquines, oxidative stress and prothrombotic markers, in non diabetic, non hypertense subjects with dysglycemia and abdominal obesity, recruited from a population at high risk of developing insulin resistance. These effects are independent of the changes in arterial blood pressure. Trial registration: NCT00319202

## Background

During the second half of the 20^th ^century the prevalence of type-2 diabetes mellitus (DM2) has increased dramatically all over the world [1]. It has been estimated that more than 171 million people suffer from this disease and that this number could increase to 366 million by 2030, of which 298 million would be from developing countries [2]. Currently, in Latin America, the DM2 prevalence ranges from 1.2% to 8%, and it is expected to increase to 38% during the next 10 years [3]. This epidemic has been related with the growing prevalence of obesity, especially abdominal [4]. Recently, we have demonstrated that the presence of cardiovascular risk factors in the Andean population is associated with a lower cut-off point of waist circumference [5,6] than the one used for Caucasian populations [7]. We have previously described that Andean population with pathologies like metabolic syndrome, hypertension and preeclampsia, all of them associated with an increased risk of cardiovascular diseases (CVD), presents higher plasma levels of inflammatory markers such as C-reactive protein (CRP) and proinflammatory cytokines [8-11].

Patients with DM2 have an increased risk of developing coronary artery disease by 2 to 4 fold and a higher risk of presenting recurrent and/or mortal cardiovascular events by 1.5 to 3 fold [12]. Based on the risk of developing micro-vascular complications, the American Association of Diabetes (ADA) reduced the threshold for DM2 to a fasting glucose level ≥126 mg/dl [13]. Moreover, the criteria of impaired fasting glucose (IFG) was defined as fasting glucose plasma level between ≥ 100 mg/dL and <126 mg/dL, and was proposed as equivalent to the impaired glucose tolerance (IGT) category obtained by oral glucose tolerance test (OGTT) [13]. Several articles have shown that patients with IFG have an increased risk of cardiovascular morbidity and mortality [14,15]. This association has been explained by the participation of hyperglycemia, especially postprandial, in the development of atherosclerosis due to metabolic and structural changes of the vascular wall [16]. In the long term, this condition may result in macrovascular alterations and in the increased risk of CVD [15]. According to these observations, our group has recently showed that patients with IFG, regardless of other traditional cardiovascular risk factors, presented a higher risk of luminal coronary disease [17].

The etiological factors of DM2 have not been totally elucidated, but it is well known that insulin resistance precedes the DM2 onset by 10 to 20 years [18,19]. Individuals with insulin resistance have impaired endothelium-dependent vasodilation and a loss of the physiological vasodilation caused by insulin [20], which is primarily due to an increased expression of the endothelial nitric oxide synthase (eNOS) [21]. It is also well known that obesity, hypercholesterolemia and diabetes are related to a reduction in flow-mediated dilation (FMD) [22,23], which is mainly caused by the endothelial production of nitric oxide (NO).

Endothelial dysfunction is a condition defined as a decrease in the production of NO and the predominance of vasoconstrictor substances that result in an increase of the the vascular tone that predisposes to a prothrombotic and proatherogenic state [24,25].

Intra-abdominal adipocytes are directly related to hyperinsulinemia and insulin resistance [26]. Hyperinsulinemia promotes the release of free fatty acids (FFA) from the adipocytes and their hepatic transformation into oxidized LDL, which has a higher atherogenic potential. Moreover, abdominal adipocytes are an important source of proinflammatory cytokines, such as tumor necrosis factor alpha (TNF-α) and interleukin 6 (IL-6) [27], that can reduce the expression and activity of the eNOS in human cultivated umbilical endothelium cells [28] which suggests that this could be one of the mechanisms by which abdominal obesity is related to endothelial dysfunction [29]. Furthermore, we have recently demonstrated that in cultured human endothelial cells, angiotensin II (AII), through its type 1 receptor (AT_1_), stimulates the TNF-α production which increases the activity of matrix metalloproteinase-2 (MMP-2)[30], enzyme that affects the endothelium structure as well as the stability of the atherosclerotic plaque [31] (Figure 1).

**Figure 1 F1:**
[figure not shown]
**title**. Physiopathological mechanisms relating abdominal adiposity, angiotensin II, insulin resistance and cardiovascular events. For description see text.**Foot note.****FFA: **Free Fatty Acids, **FAS:**, **GDPH:**, **IL-6: **Interleukine 6, **IL1β: **Interleukine 1β, **TNFα: **Tumoral Necrosis Factor α, **AI: **Angiotensin I, **AII: **Angiotensin II, **ACE**: Angiotensin Converting Enzime, **eNOS**: endothelial Nitric Oxide Sintase, **CPKII: **Creatinphosphokinase-II, **IRS-1: **Type 1 Insulin Soluble Receptor **IRS-2: **Tipe 2 Insulin Soluble Receptor, **GLUT-4:**Type 4 Glucose Membrane Trasnporter, **MMP2: **Matrix Metalloproteinase-2, **NO: **Nitric Oxide, **UPC-2: **Uncoupling Portein 2, **PPARs: **Peroxisome Proliferator-Activated Receptors, **DM2: **Tipe 2 Diabetes Mellitus, **CVE: **Cardiovascular Events, scater line: Inhibition or delay, filled line: Activation or increment.

All of them, angiotensin receptors (AT_1 _and AT_2 _types), angiotensin converting enzyme (ACE) and angiotensinogen, are widely expressed in the human adipose tissue [32,33]. Furthermore, the angiotensinogen gene expression is directly related to the degree of abdominal obesity [34]. Moreover, a direct correlation between body mass index and the circulating levels of angiotensinogen and AII has been reported [35]. These results demonstrate that the visceral adipocyte is both, a generator and a target tissue of the AII through the activation of AT_1 _and AT_2 _receptors. AII has regulatory functions in the adipogenesis and the size of the fat reservoir. Experiments *in vitro *have shown that AII indirectly induces the transformation of adipocytes precursor cells into mature fat cells [36], suggesting that this is one of the mechanisms by which AII stimulates the accumulation of the adipose tissue. In studies realized in rodents, the treatment with AII Receptor Blockers (ARBs), caused a reduction in the weight and in the size of the adipocytes independently of the food intake [37]. It is normally accepted that AT_2 _receptors are the most commonly and widely distributed receptors of AII, however, effects of AII mediated by AT_1 _receptors on the storage of triglycerides and on the activity of key lipogenic enzymes such as fatty acid synthase (FAS) and glycerol-2 dehydrogenate phosphate (GDPH) have also been demonstrated in cultured cells [38].

The increase in the production and storage of FFA induces insulin resistance through the inhibition of the transportation and phosphorylation of glucose in skeletal muscle, which produces a reduction of the glycogen synthesis and glucose oxidation rates [39]. Additionally, it has been suggested that FFA interfere with the stimulation of the expression of the glucose transporter GLUT-4 and the hexokinase activity [39]. AII and insulin share signal transduction pathways. Thus, insulin activates proteinkinase C (PKC) through the tyrosine phosphorilation of insulin receptor substrate type 1 and 2 (IRS-1 and IRS-2) and stimulates the MAP-kinase pathway signaling, whereas the AII inhibits PKC that alters the intracellular signaling of insulin [40].

All also has a stimulating effect on the transcription rate of the *ob *gene in human adipocytes, which codifies leptin, inhibiting appetite and regulating thermogenesis [41]. The sustained increase in leptin levels leads to leptin-resistance, moreover, high levels of leptin produce a greater expression of the uncoupling protein 2 (UPC-2) mediated by peroxisome proliferator-activated receptors (PPARs). UPC-2 interferes with the mitochondrial respiratory chain of the pancreatic β-cells, reducing the ATP generation and blocking the first peak of insulin secretion and favoring the onset of hyperglycemia [42]. Contrary to the results obtained in *in vitro *experiments [43], the infusion of AII to animals causes no effect over leptine expression [44]. This contradictory result could be explained by the activation of the sympathetic nervous system, which impedes the stimulating effect of AII on leptin production. Furthermore, high concentrations of leptin increase blood pressure, through sympathetic nervous activation and the sodium retention in the kidneys contributing to the development of hypertension in obese subjects [45]. The administration of ARBs in animal models, increase adiponectin plasma levels [46], which stimulate glucose utilisation and fatty-acid oxidation by activation of AMP-kinase [47]. In fact, the administration of Candesartan, an antagonist of AT_1 _receptor, to a group of hypertense subjects caused a reduction of adiponectin, C-reactive protein and markers of insulin resistance, such as the QUICKI index [48]. Furthermore, TNFα, another proinflammmatory cytokine, down-regulates the expression of adiponectin gene, impairs signal transduction of insulin in muscles [49] and it is proposed as a factor involved in the etiology of obesity related insulin resistance syndrome.

All acts also as a pro-oxidant substance by regulating the activity of the enzyme NADPH oxidase that catalyzes the production of reactive oxygen species (ROS), such as the superoxide anion and peroxynitrite[50]. ROS are substances that are directly related to the development of atherosclerotic plaque not only by inactivating NO but also by increasing the expression of cellular adhesion molecules that favor the migration of monocytes and leukocytes to the vascular wall [51] and by stimulating the growth, the remodeling and the migration of smooth muscle cells [52]. Moreover, AII has a procoagulant effect by stimulating the production of Plasminogen Activator Inhibitor-1 (PAI-1) [53], which is the principal endogenous inhibitor of fibrinolysis "in vivo" and is associated with atherosclerosis [54].

The treatment with ACE inhibitors (ACEIs) and ARBs has been shown to improve the peripheral insulin resistance in both, animal [55] and clinical models [56]. The mechanism by which the renin-angiotensin-aldosterone system (RAS) blockade has a beneficial effect on the responsiveness to insulin has not been totally clarified. Some changes in peripheral insulin sensitivity after treatment with ACEIs or ARBs might be partially mediated by changes in local blood flow to sites of glucose uptake [57]. However, a variety of non-haemodinamic effects have also been reported. In obese Zucker-type rats, it was demonstrated that the chronic administration of a selective ARBs produced a significant increase in the GLUT-4 expression in skeletal muscle, a reduction in the concentrations of plasma fatty acids and an improvement in the responsiveness to insulin [58]. Moreover AII also increases the expression of Hexokinase, a key enzyme in glucose metabolism of skeletal muscle [59].

ARBs have also been associated with an increase of the PPARγ activity [60] which plays an important role in the regulation of insulin action, by controlling the transcription of multiple genes involved in the metabolism of lipids and glucose [61]. Even in absence of AT_1 _receptors, ARBs were shown to promote the activation of PPARγ in human adipose cells, which supports the existence of additional mechanisms by which ARBs improve the responsiveness to insulin [61,62].

Some clinical trials have demonstrated that ACEI and ARBs reduce the number of new-onsets DM2 when compared with other anti-hypertensive therapies [63,64]. In the study SCOPE [65] the use of Candesartan as an antihipertensive treatment, was associated with a relative reduction in new-onset diabetes by 19% (95% IC- 2 to 42%, p = 0.09) during a mean follow-up period of 3.7 years. This result is consistent with observations in other studies using blockers of the RAS in subjects with hypertension [66] including the LIFE study that compared Losartan and atenolol [67], the ALPINE study that compared Candesartan and hydroclorotiazide HCT [68], and the VALUE study that compared Amlodipine and Valsartan[63]. Moreover, results from studies conducted in normotense subjects, like the CHARM study [69], in which ARBs, caused a reduction in new-onsets DM2, suggest that the observed effects of these medications over the development of DM2 are independent of their effects over blood pressure. However, to this day, we lack results from clinical trials aimed specifically at describing the effects of the ARBs over dysglicemia/IGT in normotense non diabetic and obese subjects.

Although the mechanisms are still speculative, the results discussed above suggest that AII produced in the adipocytes of subjects with abdominal obesity is associated with insulin resistance syndrome and dysglycemia, and support the conduction of clinical trials oriented to demonstrate the beneficial effect of ARBs in the insulin sensitivity of individuals at high risk of developing CVD and DM2.

## Hypothesis

Candesartan (32 mg/day during 6 months) has a beneficial effect on fasting plasma glucose, proinflammmatory, prothrombotic and oxidative stress markers in non diabetic, non hypertense subjects, with dysglicemia and abdominal obesity. The improvement of these markers is independent of changes in arterial blood pressure.

## Methods/design

### General objective

To evaluate the effect of Candesartan 32 mg/d during 6 months on the sensibility to insulin, the concentration of inflammatory adipoquines and the prothrombotic and oxidative stress markers in non diabetic, non hypertense subjects with dysglycemia and abdominal obesity, recruited from a population with high risk of developing metabolic syndrome and insulin resistance.

#### Specific objectives

▪ To establish the effect of the administration of Candesartan on the insulin resistance assessed through the HOMA index, fasting plasma glucose, OGTT, and HbA1c levels.

▪ To study the effect of Candesartan 32 mg/d administrated during 6 months on fasting plasma levels of adipoquines such as leptin, resistin, adiponectin, IL-6 and CRP.

▪ To evaluate the effect of Candesartan on prothrombotic markers, such as D dimer, tPA/PAI-1 ratio.

▪ To determine whether the administration of Candesartan decreases the concentration of oxidative stress markers such as plasma oxidized/reduced glutathione ratio, total oxidative capability, malonaldehyde and urinary 8-Isoprostanes.

▪ To determine whether the effects of Candesartan on the insulin sensibility, adipoquines and oxidative stress, are independent of its effect upon the blood pressure.

#### Study design

Randomized, double blind, placebo-controlled, cross-over clinical trial (Figure 2).

**Figure 2 F2:**
[figure not shown]
**title**. Study design.

#### Study treatments

▪ **Treatment A: **Candesartan 16 mg (one tablet per day) taken with breakfast during 4 weeks and then increased to the optimal dose of 32 mg/d (two tablets) during the next 20 weeks, depending on the subjects' tolerance.

▪ **Treatment B: **Placebo tablets administered similarly to treatment A, one tablet daily during 4 weeks and then 2 tablets per day during the next 20 weeks.

All the subjects will be included in a therapeutic life-style change program (TLC: educational, nutritional and exercise support) during the study.

#### Study groups

The study embraces two arms (Figure 2):

▪ **Group 1: **will receive the treatment A during the first 24 weeks and then the treatment B during the last 24 weeks.

▪ **Group 2: **will receive the treatment B during the first 24 weeks and then the treatment A during the last 24 weeks.

#### Population

Participants will be non diabetic non hypertense individuals of both genders, older than 18 years with abdominal obesity and dysglycemia and/or IGT. Inclusion and exclusion criteria are shown in Table 1

**Table 1 T1:** Selection criteria

**Inclusion criteria **
• Men and women older than 18 years of age.
• Waist circumference ≥ 90 cm in male and ≥ 80 cm in female.
• To have fasting plasma glucose between 100 and 125 mg/dL and/or OGTT at 2 hours ≥ 140 mg/dL and <200 mg mg/dL.
• Having a treatment compliance over 80% at the end of the run-in phase.
All women with bearing potential must have a secure contraceptive method. Secure method will be considered: surgical sterilization, postmenopause condition with an age greater than 45 years and a period of amenorrhea ≥ 2 years. (In premenopausal women, the use of hormonal method or two barrier contraceptive methods including 1 month after the conclusion of the active phase of study treatment).

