**Exclusion criteria**
• Prior diagnosis of type 1 or 2 diabetes mellitus, chronic or acute renal insufficiency, coronary disease clinically evident (acute myocardial infarction, chest angina, myocardial revascularization) or cardiac insufficiency, or history of prior cardiovascular events (AMI, CVD, or CABG).
• Significant chronic disease (terminal stage cirrhosis or hepatic disease or cancer) that affects the survival of patients at 24 months.
• Chronic inflammatory diseases except obesity (lupus, rheumatoid arthritis, etc.).
• Blood arterial pressure >140/90.
• Acute infection of any etiology within 4 weeks prior to the beginning of the study.
• Use of steroid hormones or NSAIDs 4 weeks prior to the beginning of the study.
• Patient enrolled in a program or treatment to lose weight, 8 weeks prior to the study entry.
• Patient requiring treatment with immunosuppressive agents, for any circumstance.
• Patient who has participated in a clinical trial in the 8 weeks prior to the study entry.
• Patient who requires a major surgical procedure during the next 12 months, after enrollment (Abdominal or thoracic surgery, vascular, neurosurgery, urologic or gynecologic surgical procedure).
• Patient with history of severe chronic gastritis or any condition of the gastrointestinal tract that may affect the absorption and/or distribution of any drug administered orally.
• Alteration of the hepatic function tests.
• Triglycerides ≥ 600 mg%.
• Serum creatinin ≥ 1.5 mg/dl or calculated creatinin clearance (Cockroft's method) less than 50 ml/min.
• History of use of psychoactive drugs or abuse of alcohol.
• Positive pregnancy test in the screening visit.
• Concomitant treatment with any other antihypertensive drug.
• Contraindication to receive treatment with Candesartan.
• Pathological alterations of aortic or mitral cardiac valves (stenosis o insufficiency) or hypertrophy cardiomyopathy.
• Denial to sign informed consent, or any mental condition that makes the patient part of a susceptible population

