### Procedures

#### Enrollment

This study will be realized in an adult population with a maximum enrollment period of one year. Screening visit will include a semi-structured interview, anthropometry and blood pressure evaluation. Eligible subjects will be scheduled one week later for "Visit A", to perform a new interview, a physical examination and to withdraw blood samples, after a 10 hour fasting period, to determine plasma glucose levels, lipid profile, hepatic and kidney function and OGTT. Those who fulfill screening criteria will be included in a run-in phase to receive placebo and the standard treatment with TLC. The patients will be blinded during this phase, which will last 2 weeks. The patients with a compliance equal or greater than 80% during this "Run in" phase will be included in the study.

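### Table 1 lets in subjects who meet one glucose limb while exceeding the upper bound of the other test, including some who are diabetic by the article's own fasting threshold

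*Protocol article*

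**What the plan says.** The Population section states: "Participants will be non diabetic non hypertense individuals of both genders, older than 18 years with abdominal obesity and dysglycemia and/or IGT". It then sends the reader to Table 1 for the selection criteria. The Hypothesis has the same target, namely "oxidative stress markers in non diabetic, non hypertense subjects, with dysglicemia and abdominal obesity", and the General objective repeats it.

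The operative glucose rule is the third inclusion criterion in Table 1: "To have fasting plasma glucose between 100 and 125 mg/dL and/or OGTT at 2 hours ≥ 140 mg/dL and <200 mg mg/dL". The only exclusion in Table 1 that concerns diabetes is "Prior diagnosis of type 1 or 2 diabetes mellitus".

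The Background gives the one diabetes threshold in the article, saying that the diabetes association "reduced the threshold for DM2 to a fasting glucose level ≥126 mg/dl".

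Under Enrollment, blood is taken at Visit A "to determine plasma glucose levels, lipid profile, hepatic and kidney function and OGTT". The next step is: "Those who fulfill screening criteria will be included in a run-in phase". No further check for diabetes is described between that point and randomisation.

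**The concern.** A rule of the form limb 1 and/or limb 2 is satisfied by either limb alone. The upper bound in each limb then limits only the test named in that limb. A subject who qualifies on the 2-hour test can have any fasting value, and the reverse. The exclusion list does not close the gap, because it looks to history and not to what the trial's own screening tests show.

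What is at stake is the population to which the result applies. The Background justifies the trial by a lack of evidence in normotensive, non-diabetic, obese people. Fasting and post-load glucose are both named within the primary endpoint in the Statistical analysis section, and fasting glucose also enters the HOMA formula, so the quantities that define eligibility are those on which the trial will report. If some participants are in the diabetic range at entry, the estimated effect is an average over a wider group than the hypothesis names.

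**Working it through.** No stated figure needs reproducing here. The check is one of eligibility logic.

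**Inputs**
- Limb 1: fasting glucose 100-125 mg/dL (Table 1, inclusion).
- Limb 2: 2-hour OGTT glucose at least 140 and below 200 mg/dL (Table 1, inclusion).
- Rule: limb 1 OR limb 2 (the and/or in the same criterion).
- Diabetes exclusion: previous diagnosis only (Table 1, exclusion).
- Fasting diabetes threshold: 126 mg/dL or more (Background).
- 2-hour bound: 200 mg/dL. The article gives this as the top of the OGTT limb and does not call it a diabetes threshold.

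**Step 1: apply the rule to every combination.** Assume no previous diagnosis and all other criteria met.

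| Fasting (mg/dL) | 2-hour <140 | 2-hour 140-199 | 2-hour ≥200 |
|---|---|---|---|
| <100 | not eligible | eligible | not eligible |
| 100-125 | eligible | eligible | **eligible, above the 2-hour bound** |
| ≥126 | not eligible | **eligible, diabetic by the Background threshold** | not eligible |

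Five of the nine cells are eligible. Two of those five lie above the upper bound of one test.

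**Step 2: one example of each.**
- Fasting 130, 2-hour 170: fails limb 1, meets limb 2, so eligible. 130 ≥ 126, so this subject is diabetic by the Background.
- Fasting 110, 2-hour 210: meets limb 1, fails limb 2, so eligible. 210 ≥ 200, so this subject is above the article's own range for the 2-hour test.

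**Step 3: how far the gap reaches.** Five cells lie above at least one bound (three with fasting ≥126, three with 2-hour ≥200, one counted in both). Three of these five are already ineligible: above both bounds, fasting ≥126 with 2-hour below 140, and 2-hour ≥200 with fasting below 100. The gap is confined to subjects who exceed one bound while the other test lies inside its own limb.

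**Step 4: apply both caps.** Adding fasting <126 and 2-hour <200 to the existing rule leaves three eligible cells: (<100, 140-199), (100-125, <140) and (100-125, 140-199). None is above either bound, and no combination that the rule is evidently meant to admit is lost.

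**The case against.** **The intent is plain.** The Population section calls participants non-diabetic in the sentence just before it refers to Table 1, and other sections agree. That stands as evidence of intent. But the Population section hands the operative criteria to Table 1, and Table 1 does not enforce the word. Blood pressure, by contrast, is enforced there by a measured limit (above 140/90), as are triglycerides and creatinine. An investigator who applies Table 1 literally would enrol the subject with 130 and 170; one who relies on the Population sentence would not.

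**A previous diagnosis could include one made at Visit A.** The exclusion does not say previous to what, and Table 2 puts Visit A at week -3 and randomisation at week 0. This reading is possible but strained, since a subject who has just met an inclusion criterion on the same visit's tests has no earlier diagnosis in the ordinary sense. At best it leaves the wording ambiguous, which also needs reconciling.

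**A journal article condenses the protocol.** That excuses missing detail. Here the rule is stated, and the stated rule conflicts with the stated population.

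**The 2-hour route is not proven.** This is right. The article never says that 200 mg/dL or more at 2 hours is diabetes, so that route is an inference from the top of the OGTT limb. The fasting route does not depend on it.

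**A reader might infer that the sample size is too small as a result.** Suppose, with inputs that are not in the article, that 5-10% of participants sit 60 mg/dL above the rest on the 2-hour test. Then SD = √(40² + p(1-p)·60²) is 42.1 at p = 0.05 and 43.9 at p = 0.10, and n = 10.507·(SD/14)² goes from 86 to 95 and 103. The article does not support this. The design is a crossover with paired tests. If subject i carries a constant offset dᵢ in both periods, the within-subject difference is (μ + τ + dᵢ + e₁) - (μ + dᵢ + e₂) = τ + e₁ - e₂, and dᵢ cancels. Putting the offset's variance into a paired formula counts variation that the design removes. It would matter only if these subjects had more variable differences or a different response, and nothing in the article bears on either. The 60 mg/dL shift also describes only the inferred 2-hour route; on the proven fasting route the 2-hour value stays at 140-199.

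**Conclusion.** The point holds as a conflict between the entry rule and the stated population. On the article's own threshold, fasting glucose of 126 mg/dL or more with a 2-hour value of 140-199 mg/dL is diabetic and eligible. By inference, fasting 100-125 with a 2-hour value of 200 or more is a second such pattern. Two of the five eligible combinations are affected.

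How many participants this means cannot be computed, because the article gives no distribution of screening values. The conclusion rests on reading and/or in its usual sense, on reading the diabetes exclusion as one of history, and on Enrollment containing no further check.

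A reader might go further and infer that the trial admits anyone with undetected diabetes, that the treatment comparison is biased, or that power is lost. The first is wrong, since three of the five combinations above a bound are already ineligible, including those above both. The second does not follow, because each subject receives both treatments in randomised order. The third fails for the reason given under the objection. The consequence is limited to whom the result describes, but the remedy is so small that the change should be made.

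**What to change.** Reconcile the Population section with both lists in Table 1. Keep the two limbs joined by and/or, and add that both Visit A values must lie below the article's own upper bounds: fasting glucose below 126 mg/dL and 2-hour OGTT glucose below 200 mg/dL. Equivalently, add an exclusion for a value at or above either bound at screening. The line should name Visit A, since the Baseline assessments section also lists an OGTT at Visit B.

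Both tests are already done at Visit A, before the run-in, so no test or visit is added. The cost is one line in Table 1 and slightly more screen failures. No change to the sample size is called for on this ground.
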